
### Limitations

3.1

Even though “Ready for Landing” is based on the current research on sleep interventions, this study as well as the intervention itself have some limitations. Firstly, due to its design, the study does not include a follow-up yet. Although this is planned for future studies, currently the control group receives the intervention at the timepoint T1 (See Figure 1) immediately after the completion of the questionnaires. We use this approach to assure they can benefit from the intervention as well before leaving the day clinic. To further account for the circumstance of frequently changing patient groups, the intervention is limited to only two sessions. This raises the question if this is enough time to thoroughly introduce and establish new sleeping habits. It may be necessary to consider, whether a longer version with more sessions of “Ready for Landing” is necessary to achieve a relevant improvement in sleep. Alternatively, a continuation in individual therapy to further support the implementation of new sleep routines could also be established and evaluated. Another limitation regarding the study design might be the waitlist design which might cause bias, delayed effects and possible confounding effects like seasonal effect regarding light and temperature or holidays. The potential negative influence of the waitlist design should be minimized by the short duration and delay when comparing the conditions.

Second, there is no screening mechanism to rule out if the sleep problems or diminished sleep quality have a somatic cause, such as obstructive sleep apnea or restless legs syndrome. For instance, a study by Andersen et al. (2019) showed that among children and adolescents 9.1% of the participants with a healthy body weight (Body Mass Index Standard Deviation Score (BMI SDS) ≤ 1.28) showed obstructive sleep apnea, while overweight children (BMI SDS > 1.28) even showed a prevalence of 44.6%. A Thai study found that 18.2% of children with ADHD referred to a psychiatric clinic showed signs for high-risk obstructive sleep apnea (Prajsuchanai et al., 2022). These findings suggest potentially higher prevalence of obstructive sleep apnea for children with psychiatric disorders. For those affected, sleep-disordered breathing might partially or completely explain insufficient sleep quality and its influence on overall wellbeing.

Regarding the intervention itself, the following limitations might be taken into consideration: the short and generic character of the intervention does limit its ability to treat, possibly undiagnosed, sleep disorders, such as primary insomnia. Concerning this matter, studies showed that sleep hygiene interventions are less efficacious compared to CBT-I which remains gold standard to treat insomnia (Chung et al., 2018; Deutsche Gesellschaft für Kinder-und Jugendpsychiatrie, Psychosomatik und Psychotherapie e.V. (DGKJP), 2018). Nevertheless, as mentioned above, by incorporating CBT-I elements we hope to further improve efficacy and therefor add a value that exceeds stand-alone psychoeducation, to aim for a significant improvement in sleep quality and elongation of sleep duration. In terms of content, the airplane landing metaphor, which is supposed to illustrate the process of going to sleep, might not help some to understand the underlying context. Not all children and adolescents have experienced a passenger flight themselves. It is essential to ensure that along explaining the metaphor, the sleep hygiene rules are explained clearly as well. Patients more so have to be encouraged to ask questions if the concept remains unclear. Further group therapy format limits the options to discuss specific sleep problems in depth. Participants are invited to talk about their specific and possibly unaddressed sleep problems at the end of the intervention. We further hope increasing awareness about the necessity of restorative sleep might bring sleep and sleep problems into focus, which are then addressed in individual therapy if needed. Concerning the setting, it also has to be discussed on how to transfer “Ready for Landing” to different settings such as individual or inpatient treatment. Especially with inpatient treatment it has to be examined, if rules, such as only using the bed to sleep, are possible to implement in the current layout of treatment facilities. In those more restrictive environments, there is a need to come up with treatment concepts that enable a good sleep hygiene and that ensure patients can autonomously build those new habits.

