### Study design

2.1

The study is conducted using a waitlist-control-design. Each participant attends three sessions in a group therapy setting, with session T0 and T1 forming the primary focus to detect a treatment effect (Figure 1). The third timepoint, T2, serves for further exploratory analysis and to deliver the intervention to the control group as well. Two out of three sessions are the RfL-sessions, while a third one is of an unrelated topic. Participants are quasi-randomized into intervention or control group. Allocation of participants to the group is based on the time they begin treatment in the facility. Whether the participants belong to the control or intervention group is determined by the alternating nature of their occurrence. After an intervention group lasting 28 days an about 8–10 weeks pause interval follows to reach a sufficient amount of new, naive-to-the treatment admissions. After that a control group of 28 days starts, also followed by an 8–10 weeks pause interval afterwards. This process, alternating between intervention and control group with an 8–10 weeks pause interval in between, is continued until the required number of participants has been reached. Participation from start to end lasts 28 days representing 4 weeks around the described timepoints. The measurements collected for this study consist of different self-report questionnaires, sleep logs and actigraphy data. Psychometric properties of the questionnaires used are described below.

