**Figure 1 fig1:**
[figure not shown]
Study design “Ready for Landing” (RfL). Participation consists of 3 sessions in both conditions. The intervention group starts with the two RfL sessions and finishes with intervention-unrelated group therapy while the control group starts with the intervention-unrelated group therapy and then receives the RfL intervention. Intervention and control group are conducted in consecutive, alternating turns separated by an 8–10 weeks pause interval.

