The intervention consists of two 90-min sessions held 1 week apart from each other. In the intervention group those sessions take place at T0 and T1, the control group undergoes the intervention at T1 and T2. To give patients as much control as possible over their sleep routine, the intervention is implemented in day-clinic treatment settings for children and adolescents in psychiatric care. During the first session, patients learn about the functionality of healthy sleep, reflect on their own current sleep quality, sleep habits, and sleep hygiene and are introduced to the airplane metaphor. The metaphor explains sleep hygiene as a well-structured and segmented process consisting of different phases which enable pilots to land the plane safely, in other words to establish a good routine to go to sleep and is depicted in Figure 2. The landing of a passenger airplane is described to pass through 12 stages which are grouped into four phases: flight schedule, descent, landing approach and park position. In the “flight schedule” phase, consistent times for departure, as well as preparations regarding the takeoff and the flight itself are outlined. During “descent” service of food and beverages is stopped and passengers must remain seated. The patients are further advised not to take naps 3 h before bedtime. According to the common sleep hygiene recommendations it is emphasized not to nap after 3 p.m. The difficulty, however, was that the day clinic treatment was not finished until around three o’clock. In order to address this important rule, therefore the time window had to be adjusted accordingly (no nap 3 h before bedtime). Although the time stated on the poster may seem too late, it was pointed out during training that it was important not to nap too late and certainly not 3 h before bedtime.” During the third phase, the “landing approach,” electronic devices have to be turned off (“flight mode”), passengers are told to sit back and relax and in case of turbulences or obstructions on the runway a loop is flown and landing is restarted shortly after. The fourth phase mainly targets the processes occurring when the plane landed and is pulled into its hangar. It is therefore named “Take park position” and describes the importance of a clean and functional but also welcoming hangar which is used for this purpose only. Each phase corresponds to a specific time window. The first phase mainly describes the day starting with getting up and ending with the time to start preparing for bedtime. The second phase, “descent,” covers 3 h before bedtime while the third phase, “landing approach,” comprises of the last 30 min before the planned bedtime. Phase four, “Take park position,” mainly consist of the night and daytime preparations making sure the sleeping place is ready when it needs to be.

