#### Questionnaires and actigraphy

2.1.2

The study aims to detect improvement in subjective and objective domains of sleep following the intervention. Subjective sleep quality is assessed using PSQI (Buysse et al., 1989). The PSQI consists of 24 items covering seven domains of sleep quality including sleep quality, sleep latency, sleep duration, sleep efficiency, sleep disturbances, use of medication, and daytime sleepiness. The PSQI is a validated and widely used self-report measure for sleep quality showing good reliability, internal consistency, criterion validity and discriminatory power. A global score of five has been deemed sufficient to discriminate between good and bad sleep quality (Buysse et al., 1989). Those findings have been replicated for the use of the PSQI in minors (La Vega et al., 2015; Larche et al., 2021). To assess daytime sleepiness, we use the Epworth Sleepiness Scale for Children and Adolescents (ESS-CHAD, Janssen et al., 2017) which consists of eight items regarding the tendency to fall asleep during different age-adjusted daytime activities such as during lessons in school. The ESS-CHAD has been shown to be a reliable and valid measure to assess daytime sleepiness in minors (Janssen et al., 2017). Both questionnaires were chosen because they are applicable to our wide age range from 10 to 18 years of age likewise and are commonly used in sleep research. This ensures comparability within the group of participants and also allows to compare our results to those of other researchers. PSQI and ESS-CHAD are distributed at the beginning of every session so that the participants answer them before they receive any new elements of the intervention during the sessions. They are instructed to focus on symptoms present in the last week. Between sessions the patients keep a sleep log that monitors aspects such as bedtime, waketime, total sleep duration, duration until they fall asleep and subjective aspects such as perceived rest-and wakefulness each day during the week. Those subjective measures will be complemented by actigraph data to gain insides about possible incremental validity. The comparability of subjective and objective sleep data collected in this study will be subject of another study. Hence, this will be described in an additional study protocol, which aims to gain insight on subjective and objective measurements of sleep in youth with mental health problems.

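### The short T0–T1 window does not control an abrupt holiday change between the two compared weeks, because at each clinic the two arms run in different calendar periods

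*Protocol article*

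**What the plan says.** Section 2.1 (Study design) describes turns "alternating between intervention and control group with an 8–10 weeks pause interval in between", and the Figure 1 legend confirms that the arms follow one another rather than run side by side: "Intervention and control group are conducted in consecutive, alternating turns separated by an 8–10 weeks pause interval". The arm is fixed by calendar time: "Allocation of participants to the group is based on the time they begin treatment in the facility". Section 2.5 starts a turn once enough patients have been admitted.

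Section 2.1.1 puts the two intervention sessions one week apart, at T0 and T1 in the intervention arm. Section 2.1.2 has the PSQI and the sleepiness scale filled in at the start of each session, about the preceding week: "They are instructed to focus on symptoms present in the last week". Actigraphy runs through the whole 28 days. Section 2.9 tests the effect with a repeated measures ANOVA on GROUP and TIMEPOINT at T0 and T1.

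Section 3.1 (Limitations) concedes "possible confounding effects like seasonal effect regarding light and temperature or holidays" and then states: "The potential negative influence of the waitlist design should be minimized by the short duration and delay when comparing the conditions".

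**The concern.** A waitlist control removes calendar effects when both arms are observed in the same weeks. Here, at a given clinic, they are not. The primary contrast compares the change from the week before T0 to the week between T0 and T1 in one calendar period with the same change in another period about three months away.

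Slow trends in light and temperature move little from one week to the next, so they largely cancel in the T1−T0 change. The start or end of school holidays is different, because it is a step. If it falls inside the two weeks, all participants of that turn may shift bed and wake times in the same direction. That shift goes into the GROUP × TIMEPOINT term of whichever condition the turn belongs to. It could pass for an intervention effect or hide one, on both the PSQI and actigraphic sleep time. The reassurance in section 3.1 treats season and holidays alike, and for the second it is incomplete.

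**Working it through.** **Inputs from the protocol article.** Turn length 28 days and pause 8–10 weeks (2.1); sessions one week apart (2.1.1); look-back of one week (2.1.2); two-factor ANOVA at T0 and T1 (2.9); effect size 0.25, power 0.90, alpha 5%, N = 46 (2.4); three day clinics (2.2). The one-week T0–T1 interval is stated for the intervention arm and inferred for the control arm.

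**Inputs assumed, because the documents give none.** 6–12 abrupt calendar boundaries a year; a step of 30–60 min in sleep time; SD of change 60 min; two equal turns per arm; correlation between T0 and T1 of 0.5.

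**1. The plan's own figure.** With two groups, two measurements, f = 0.25 and rho = 0.5: lambda = f² × N × m/(1 − rho) = 0.0625 × 46 × 2/0.5 = 11.5, on 1 and 44 degrees of freedom. Power is 0.912, so N = 46 reproduces. The 0.25 is printed as d, but reading it as d (f = 0.125) would need N = 172 at rho = 0.5. The planned effect is therefore f = 0.25. At rho = 0.5 the SD of change equals the SD of the outcome, and a between-arm difference in change D gives D² × 46/4 = 11.5, so D = 1.0 SD. That is the benchmark used below.

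**2. Separation of the arms.** Start to start: 4 + 8 = 12 to 4 + 10 = 14 weeks. At one clinic, opposite arms share no calendar week.

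**3. How often a boundary is met.** The two compared weeks are 14 nights with 13 night-to-night transitions. Expected boundaries per window: 13 × 6/365 = 0.21 to 13 × 12/365 = 0.43.

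**4. How much of the step enters the change.** If the step comes after night k, its weight in the difference between the weekly means is k/7 for k = 1 to 7 and (14 − k)/7 for k = 8 to 13. The weights sum to 28/7 + 21/7 = 7, so the average is 7/13 = 0.54. The weight is 1 only at k = 7, that is, at T0.

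**5. Shift in the arm mean when one of two equal turns is affected.**

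| Position of the step | 30 min step | 60 min step |
|---|---|---|
| Exactly at T0 | 0.5 × 30 = 15 min (0.25 SD) | 0.5 × 60 = 30 min (0.50 SD) |
| Average over positions | 15 × 7/13 = 8 min (0.13 SD) | 30 × 7/13 = 16 min (0.27 SD) |

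Against the planned 1.0 SD this is 25–50% at worst and 13–27% on average.

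**6. Effect on the test, given that a boundary is met.** This was simulated with 23 per arm, a t test on change scores (equivalent to the interaction F test) and 40,000 runs, with the step on half of one arm.

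| Step, in SD of change | Rejection under no effect (nominal 5%) | Power when the step favours the control arm |
|---|---|---|
| none | 5% | 91% |
| 0.25 | 7% | 82% |
| 0.5 | 13% | 68% |
| 1.0 | 37% | 31% |

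A 30–60 min step at full weight is 0.5–1.0 SD (last two rows). At the average weight it is 0.27–0.54 SD, close to the 0.25 and 0.5 rows. With only a third of one arm affected, rejection under no effect is 6%, 8% and 18% for steps of 0.25, 0.5 and 1.0 SD.

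**The case against.** The authors disclose holidays themselves and claim only that the influence should be minimised, not removed. Their argument has force: by step 3, the chance of meeting a boundary grows with the length of the window, so a short window does reduce exposure. A reader might infer that the short window makes matters worse. It does not; it makes a boundary less likely, and most positions dilute the step.

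A reader might also infer that a boundary necessarily falls on one arm only and can never be separated from the intervention. That is exact for one turn at one clinic. There are three clinics, however, and the article does not say whether their turns are synchronised, so another clinic might run the other condition in the same weeks. Over several turns each arm may also meet its own boundaries, but balance by chance comes slowly. If every turn had its own random shift with an assumed SD of 0.3, rejection under no effect would be 16% with two turns per arm, 12% with three and 10% with four.

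A third tempting reading is that the shift equals or exceeds the planning effect. That takes the printed d = 0.25 at face value, and N = 46 does not support it (step 1).

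The size of the step is unknown and may be small. Attendance at the day clinic until about three o'clock may anchor wake times, and the requirement of continuous treatment makes a clinic closure between the two weeks less likely. Clock changes are not mentioned in the document, and the point does not need them. Finally, a scheduling rule or a calendar term may stand in a fuller protocol or analysis plan, so their absence from the article is not the fault. What remains is the statement in 3.1, which offers a protection that the described design gives only in part.

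**Conclusion.** The point holds in limited form. The short T0–T1 window protects against slow seasonal drift and lowers the chance of meeting a holiday boundary. It does not remove a boundary that falls within the 14 nights, because no concurrent control at that clinic subtracts it.

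Under the assumptions listed, the bias in an affected arm mean is at most 0.25–0.50 SD and about 0.13–0.27 SD on average, against a planned difference of about 1.0 SD of change. This is enough to disturb the primary test when it happens, but not enough to replace the planned effect. Steps below 30 min, or more turns per arm, would matter less. The step size, its frequency, the SD of change, the number of turns and rho are all assumptions. The non-concurrence at each clinic, the adjacent-week contrast and the wording of 3.1 come from the document, apart from the inferred one-week interval in the control arm. The change is worth making because it costs little.

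**What to change.** 1. In 2.1 and 2.5, where the 8–10 week pause allows, choose T0 at each clinic so that the week before T0 and the week from T0 to T1 lie in the same school-term or holiday period.
2. Record the holiday status of both weeks for every turn at every clinic, and pre-specify a sensitivity analysis of the primary outcomes that leaves out turns straddling a boundary.
3. In 3.1, limit the reassurance to slow seasonal trends and say that abrupt calendar changes are not controlled by the short window.

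Cost: a calendar check per turn and some protocol wording, with no extra measurements. The pause gives only two weeks of room (10 − 8), so not every boundary can be avoided, and moving a start may miss a few eligible patients. The sensitivity analysis loses precision because it may drop a whole turn, which is half an arm if there are only two turns per arm. It should therefore support the primary analysis, not replace it.

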### Further directions

3.2

If proven efficacious, we aim to provide “Ready for Landing”—including its manual and materials—available for implementation by other professionals. Furthermore, we aim to examine the intervention’s feasibility in other contexts than day clinic treatment, such as inpatient or outpatient treatment groups, or educative programs with healthy youth. Potentially we could further aim to investigate its efficacy regarding specific disorders and explore different age groups.

## Conclusion

4

In conclusion the study aims to evaluate the efficacy of a sleep hygiene intervention for children and adolescents with psychiatric disorders, on both, objective and subjective measures of sleep quality, and sleep duration. “Ready for Landing” conveys the principles of sleep hygiene through the metaphor of a landing passenger airplane, describing a well-structured process. The intervention consists of different phases and uses psychoeducative as well as cognitive-behavioral elements. The program is developed to be implemented as a group therapy-based intervention with two sessions for children and adolescents aged 10–18 years in day clinic treatment. It is hypothesized that the intervention is capable to improve sleep quality and elongate sleep duration. If “Ready for Landing” shows to be efficacious, it could offer a simple and cost-effective treatment option to help bridge the gap between highly prevalent sleep problems in children and adolescents suffering from mental health problems and the often-unmet therapeutic needs.
